Participants with recurrent NP will be recruited from the community in Birmingham and in Essex. The recruitment process will aim to reflect the real-world distribution of NP occurrences between sexes. Given the 2:1 ratio of NP prevalence in favour of females,^42^ we expect that the recruitment process will result in a proportional sample that mirrors this difference. Due to the use of questionnaires and standardised procedures in the evaluation of candidate predictors and outcomes, only people able to understand or follow study procedures will be recruited. Participants for the control group will only be recruited from the community in Birmingham, and we will ensure comparable demographic characteristics to those within the recurrent NP cohort. Participants will be recruited from the University of Birmingham and University of Essex staff/student population and Birmingham’s/Essex’s local community. Recruitment methods will include printed hard copy advertisements with researchers’ emails pasted throughout the campus within the University of Birmingham and University of Essex, and identical soft copy advertisements disseminated using the University’s intranet and email system, social media platforms such as Facebook and *X,* and via word of mouth. Additionally, NIHR Research Delivery Network support will allow us to recruit participants with recurrent NP through the NIHR 'Be Part of Research’ service.

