### Prognostic variables of pain recurrences

#### Baseline laboratory assessment

All recruited participants with a history of recurrent NP episodes will attend an initial laboratory session (in Birmingham or Essex) during a period of symptom remission, and a battery of tests will be conducted to obtain a comprehensive evaluation (table 1). To minimise inter-site variability, all assessments will follow a standardised protocol, and both laboratories will use identical equipment from the same manufacturer. Participants will also be asked to complete a series of questionnaires to assess psychological features, including the Depression, Anxiety and Stress Scales (DASS-21),^43^ the short version of the Tampa Scale for Kinesiophobia (TSK-11),^44^ the EQ-5D-5L^45^ and pain processing characteristics, including the pain-self efficacy questionnaire,^46^ pain coping inventory^47^ and central sensitisation inventory.^48^ Overall, we will collect information on demographic characteristics, psychological and social factors, pain processing, neck kinematics, neck sensorimotor control and neck muscle function.

**Table 1 T1:** Collected data within physical, psychological and social domains

Domain	Feature extracted	Measurement tool
Demographics and Neck Pain characteristics	Age Sex BMI Ethnicity Number of other pain sites Number of previous pain episodes	Single question for each feature
Psychosocial factors	Stress (0–21) Anxiety (0–21) Depression (0–21) Kinesiophobia (11-44) Quality of life (0–100) Occupation Education level	DASS-21 DASS-21 DASS-21 TSK-11 EQ-5D-5L Single question Single question
Pain processing	Self-efficacy (0–60) Pain coping (12–48 active, 22–84 passive) Central sensitisation (0–100) Pressure pain threshold (kPa) Conditioned pain modulation	Pain Self-Efficacy Questionnaire Pain Coping Inventory Central sensitisation inventory Pressure algometry Cuff pressure algometry
Kinematic features and sensorimotor control	Average range of neck motion in flexion-extension, lateral flexion (R/L), rotation (R/L) Average speed of neck movement in flexion-extension, lateral flexion (R/L), rotation (R/L) Smoothness of neck movement (Jerk Index) in flexion-extension, lateral flexion (R/L), rotation (R/L) Neck proprioception (joint reposition error during right and left rotation)	All features obtained using wearable Inertial Measurement Unit (IMU, Sensamove 3D Cervical Trainer)

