##### Neck kinematics

A wearable Inertial Measurement Unit (IMU) system (myoMOTION Research Pro, Noraxon USA Inc.) with a sampling rate of 100 Hz will be used to analyse cervical kinematic outcomes while sitting. The IMU sensors will be placed via double-sided tape on the forehead and upper thoracic spine (T1). Participants will be asked to perform their active neck movements as far as they comfortably can go (flexion/extension, rotation, side flexion; randomised order using random number generator). Movements will be self-paced. They will be asked to do three repetitions for each plane of movement. One minute of rest will be provided between the different directions. The following features will be extracted: range of motion, speed of motion and smoothness of movement, measured by analysing the jerk index during active cervical movements.^54^ IMU sensors have high concurrent validity and reliability in the assessment of neck movements.^55^,^57^

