### Data analysis plan

#### O.1 Identification of candidate predictors

To identify candidate predictors that are clinically relevant, we will conduct two different comparisons. First, we will assess at baseline physical, psychological and social features during a period of remission and compare them with normative values from a control group using an independent t-test if the data satisfy parametric assumptions, or a non-parametric test, such as the Mann-Whitney U test, if they do not. Additionally, collected features within the physical and psychological domains will be assessed during a pain episode to evaluate the impact of pain on them. Comparisons with baseline (without pain) will be conducted using a paired t-test or a non-parametric alternative such as the Wilcoxon signed-rank test for within-subject comparisons. Differences will also be quantified by mean differences and 95% CIs. Physical, psychological and social features that differ between groups or within the same subject (during remission and pain episode) will then be considered as candidate predictors. Importantly, only baseline values of the candidate predictors collected will be used for prediction model development.

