
### Sample size

#### Sample size estimation for identification of candidate predictors (O.1)

Potential candidate predictors will be identified after testing physical and psychosocial factors for between-subject and within-subject differences. To consider a feature as a potential predictor, we expect a moderate effect size both for the comparison between subjects and within subjects. For the between-subjects analyses, we will consider 48 participants for the control group and 96 for the recurrent NP group. The sample size has been determined through a power analysis (G*Power), which assumes a moderate effect size of 0.5, an alpha level of 0.05 and a beta level of 0.8, with an allocation ratio of 2:1. For the within-subject comparison, we will conduct the second lab assessment on 34 participants with recurrent NP during an acute episode (α=0.05 and β=0.8).

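### Controls come only from Birmingham while cases are tested in Birmingham or Essex, so the unadjusted O.1 group comparison cannot separate a case-control difference from a laboratory difference

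*Protocol article*

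**What the plan says.** Under Participants and recruitment, the article says of the cases: "Participants with recurrent NP will be recruited from the community in Birmingham and in Essex". Of the comparison group it says: "Participants for the control group will only be recruited from the community in Birmingham". The same sentence adds that controls will be demographically comparable with the cohort. Under Baseline laboratory assessment, the cases "will attend an initial laboratory session (in Birmingham or Essex) during a period of symptom remission"; that section also promises one standardised protocol and identical equipment at both laboratories.

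The O.1 analysis section will take baseline features and "compare them with normative values from a control group using an independent t-test if the data satisfy parametric assumptions", with Mann-Whitney as the alternative. The decision rule follows: "features that differ between groups or within the same subject (during remission and pain episode) will then be considered as candidate predictors". No site term appears.

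The O.1 sample size section says "we will consider 48 participants for the control group and 96 for the recurrent NP group", for an effect size of 0.5, alpha 0.05, a 2:1 ratio and 80% power (printed as a beta level of 0.8). The O.2 sample size section aims for 300 cases over the two sites and does not give the split.

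**The concern.** Every Essex participant is a case. If a feature reads systematically higher or lower in Essex, that shift enters the case mean and not the control mean, and a two-sample test attributes it to neck pain history.

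Some measurements depend on the tester: the dynamometer is held by the assessor for neck flexion and extension, and the investigator resists the shoulder shrug. Identical equipment does not standardise the person holding it. The two source communities may also differ in ways that demographic comparability does not capture.

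The stake is the candidate list. The article allows about 16 candidate predictors with 250 participants. A feature selected because of laboratory takes one of those places, and a true difference masked by an opposite shift may not enter through this route.

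**Working it through.** **Inputs from the article:** 48 controls, Birmingham only; 96 cases in the O.1 power calculation; 300 cases in total; effect size d = 0.5; alpha 0.05.

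**Assumptions, because the article gives no figure:** Essex share of cases f = 1/3 or 1/2; between-laboratory shift s = 0.1 to 0.5 SD; controls tested only in Birmingham (implied by their recruitment, not stated).

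**Step 1. The article's own figure.** For a two-sided t-test the noncentrality is d / √(1/48 + 1/96) = 0.5 / 0.1768 = 2.83 on 142 degrees of freedom, giving power 0.802. With 47 and 94 it is 0.794. The stated 48 and 96 reproduce.

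**Step 2. False selection.** With no true group difference, the expected case-control difference is f × s. For f = 1/2 and s = 0.3 it is 0.15 SD, and the noncentrality is 0.15 / 0.1768 = 0.85 with 96 cases, or 0.15 / √(1/48 + 1/300) = 0.15 / 0.1555 = 0.96 with 300. Simulated rejection rates of the unadjusted t-test (nominal 5%) are:

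| Shift s | 96 cases, f = 1/3 | 96 cases, f = 1/2 | 300 cases, f = 1/3 | 300 cases, f = 1/2 |
|---|---|---|---|---|
| 0.1 SD | 5% | 6% | 6% | 6% |
| 0.2 SD | 7% | 8% | 7% | 10% |
| 0.3 SD | 8% | 13% | 9-10% | 16% |
| 0.5 SD | 15% | 28% | 17-18% | 34% |

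More cases make it worse, because the bias f × s stays fixed while the standard error shrinks.

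**Step 3. Masking.** With a true d = 0.5, 96 cases and f = 1/2, an opposite shift leaves an expected difference of 0.5 − f × s. At s = 0.3 this is 0.35 SD (noncentrality 0.35 / 0.1768 = 1.98), so power falls from 80% to about 50%. At s = 0.5 it is 0.25 SD, and power is about 28%.

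**Step 4. The remedy.** In a model of feature on group and site, with controls at one site only, the group coefficient equals the Birmingham case mean minus the Birmingham control mean. The laboratory component drops out. Power at d = 0.5, taking the Birmingham participants alone:

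| Cases entering | Essex share | Comparison | Power |
|---|---|---|---|
| 300, unadjusted | any | 48 v 300 | 89% |
| 300 | 1/3 | 48 v 200 | 87% |
| 300 | 1/2 | 48 v 150 | 85% |
| 96 | 1/3 | 48 v 64 | 74% |
| 96 | 1/2 | 48 v 48 | 68% |

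The planned 80% is kept with at least 96 Birmingham cases, which is 96 / 300 = 32% of the cohort.

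**The case against.** The article has safeguards, and they count. A common protocol and identical equipment make small shifts plausible, and at 0.1 SD the inflation is negligible. Comparable demographics deal in design with much of what age and sex adjustment would do, so the absence of those covariates is mainly a question of precision.

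O.1 is also a screen and not the model. Controls never enter the prediction models. LASSO, if it is the approach used, can drop a spurious candidate. The within-subject comparison (unaffected if both visits use the same laboratory) and the systematic-review evidence are other routes to candidacy. All of this stands and limits the harm.

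Other mitigations do not reach the problem. Repeating O.1 inside the bootstrap carries the same site imbalance into every resample. The check of performance by region, where possible, concerns the finished models. Nor is this detail deferred to an analysis plan: the article itself names both the tests and the source of controls.

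Two stronger readings are tempting but unsupported:

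- **Different devices at the two sites.** Table 1 has "All features obtained using wearable Inertial Measurement Unit (IMU, Sensamove 3D Cervical Trainer"), while the Neck kinematics section has "A wearable Inertial Measurement Unit (IMU) system (myoMOTION Research Pro, Noraxon USA Inc".). A reader might infer that the laboratories use different systems. The article says that both use identical equipment, so this is a separate naming inconsistency and not evidence of a site difference.
- **A cap of 96 cases.** The 96 comes from a power calculation. The O.1 analysis section contains no such restriction, and the article does not say which laboratory would supply the 96. If all were from Birmingham, the confounding would disappear.

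**Conclusion.** The concern holds as a weakness in the O.1 between-group screen. The article fixes a one-site control group, a two-site case group and a test that cannot separate group from laboratory. The confounding follows from the text; its size does not. The selection rates rest on assumed Essex shares and shifts, and range from almost no inflation at 0.1 SD to 15-34% at 0.5 SD, with a matching loss of power when the shift runs the other way.

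A reader might go further and infer that the final prediction models will be biased by site. The article does not support that: the demonstrated effect is on which features become candidates, and no effect on the finished models has been estimated. The change is worth making because it is cheap, but the study does not depend on it.

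**What to change.** In the O.1 analysis section, replace the unadjusted two-sample test with a linear model of each feature on group and site (rank-based or robust where needed), and select on the adjusted group coefficient. Comparing Birmingham cases with Birmingham controls is nearly equivalent. The two should not be presented as independent checks on each other, because without further covariates they estimate the same contrast. Age and sex may be added for precision; both are already collected.

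State that all available baseline participants enter, and that 96 is a minimum for power and not a limit. Report the Birmingham-Essex difference among cases for each feature, so that readers can see how large the shift is. The bootstrap should repeat the revised screen.

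The cost is wording, plus some power: about 85% instead of 89% at d = 0.5 if half of 300 cases are from Birmingham. If only 96 mixed-site cases entered, half from Essex, it would be about 68%, which is why the full cohort should be used. No added recruitment or testing is needed provided that Birmingham supplies at least 96 cases.

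Separately, reconcile the device named in Table 1 with the one named in the Neck kinematics and Cervicocephalic relocation test sections.

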##### Maximal and submaximal voluntary contractions

The same handheld dynamometer and surface electromyography system will be used to measure neck muscle activity during maximum and submaximal neck flexion and extension contractions. The activity of the sternocleidomastoid and splenius capitis muscles will be detected using surface electrodes with a fixed 2 cm interelectrode distance and placed bilaterally following guidelines for electrode placement.^65^,^67^ Flexion and extension isometric forces of the neck muscles will be assessed with the participants seated with their back supported and their torso firmly strapped to the seat back. Participants will be instructed to perform maximal neck flexion and extension against the dynamometer held by the assessor at the forehead and occiput respectively. Electromyographic measures of the superficial neck muscles have been shown to be reproducible and can discriminate between individuals with and without NP.^32 68 69^

Maximal isometric contraction while seated: following a period of familiarisation with the device, participants will be asked to perform two maximal contractions for both flexion and extension, which will be done in a random order. Each contraction will last 3–4 s, with 1 min rest between each repetition. The highest value for each direction will be considered as the reference maximum voluntary contraction (MVC) in order to calculate the submaximal force value. EMG signals will be recorded.

Submaximal contraction while seated: after 5 min of rest, participants will perform one submaximal isometric contraction in flexion and one in extension (order randomised for each participant) at 40% of MVC for 20 s. 5 minutes of rest will be provided between contractions. EMG signals will be recorded. Participants will be asked to rate their exertion using the Borg CR10 Scale (0–10) immediately following the completion of each sustained submaximal contraction.

Finally, participants will be asked to perform a shoulder shrug to measure the maximal voluntary contraction of the upper trapezius. The dynamometer will be placed over the participant’s acromion region by the investigator, who will resist the force exerted by the participant while they shrug their shoulder. Participants will be asked to perform two maximal contractions for each side, and the order will be randomised.

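### The O.1 group comparison has Birmingham-only controls but does not restrict or adjust for the site of the recurrent-NP participants, so any remaining Essex–Birmingham difference would be read as an effect of neck-pain history

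*Protocol article*

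**What the plan says.** All statements are in the protocol article.

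- *Participants and recruitment*: "Participants with recurrent NP will be recruited from the community in Birmingham and in Essex". For the comparison group, "Participants for the control group will only be recruited from the community in Birmingham", with the assurance that "we will ensure comparable demographic characteristics to those within the recurrent NP cohort".
- *Baseline laboratory assessment*: the recurrent-NP participants "will attend an initial laboratory session (in Birmingham or Essex) during a period of symptom remission". The stated safeguard is: "To minimise inter-site variability, all assessments will follow a standardised protocol, and both laboratories will use identical equipment from the same manufacturer".
- *O.1 Identification of candidate predictors*: the analysis will take the baseline features and "compare them with normative values from a control group using an independent t-test", or a Mann-Whitney test where parametric assumptions fail. A feature that differs between groups, or within subject between remission and a pain episode, becomes a candidate predictor. The within-subject comparison covers physical and psychological features only.
- *Sample size estimation for O.1*: 48 controls and 96 recurrent-NP participants, effect size 0.5, alpha 0.05, 2:1 allocation. The site of the 96 is not stated.
- *O.2 Development and internal validation*: region appears only as a fairness check on the finished models.

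**The concern.** With no Essex controls, a comparison that pools cases from both sites sets a two-site group against a one-site group. Whatever separates Essex from Birmingham is then partly counted as a consequence of neck-pain history.

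Two sources could produce such a difference. One is the assessor: maximal neck force, for example, is measured "against the dynamometer held by the assessor at the forehead and occiput", and the pressure algometer is a further instrument used by an examiner. The other is the local population, in features such as mood, occupation or education. The same protocol and equipment at both laboratories reduces the first source but does not remove differences between assessors. Demographic comparability only partly addresses the second.

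Two things are at stake. O.1 interprets these differences as the mark of recurrent neck pain. It also fills the candidate list for both prediction models, which has room for about 16 parameters.

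**Working it through.** **Inputs from the protocol article.** 48 controls, all from Birmingham; 96 recurrent-NP participants; d = 0.5; alpha = 0.05; 80% power; 34 participants for the paired comparison; 300 recurrent-NP participants over two sites.

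**Inputs assumed.** Essex share of the cases, p = 30% or 50%; Essex-minus-Birmingham shift, s = 0.3 SD; a feature passes when two-sided p < 0.05. The document gives neither p nor s.

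**Step 1: reproduce the plan's figure.** The two-sided noncentral t with n = 48 and 96 and d = 0.5 gives power 80.2%, so 48/96 is confirmed. A one-sided test would give 87.9%, so the calculation is two-sided. A paired t-test with d = 0.5 needs 34 participants, as stated.

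**Step 2: the bias.** The case mean is (1 − p) × Birmingham mean + p × Essex mean, and the control mean is Birmingham only. The contrast is therefore shifted by p × s:

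- p = 0.3, s = 0.3: 0.09 SD
- p = 0.5, s = 0.3: 0.15 SD

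**Step 3: false admission when there is no true difference.** Pooling two sites gives the case group variance v = 1 + p(1 − p)s², and SE = √(1/48 + v/96). The rejection probability is 1 − Φ(1.96 − bias/SE) + Φ(−1.96 − bias/SE).

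| p | s | v | SE | bias/SE | Passes |
|---|---|---|---|---|---|
| any | 0 | 1 | 0.177 | 0 | 5.0% |
| 0.3 | 0.3 | 1.0189 | 0.177 | 0.51 | 8.0% |
| 0.5 | 0.3 | 1.0225 | 0.177 | 0.85 | 13.5% |

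The noncentral t gives 8.0% and 13.4% for the last two rows.

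**Step 4: wrongly missing a feature.** With a true d = 0.5 and an opposing shift (p = 0.5, s = 0.3), between-group power falls from about 80% to about 50%. A physical or psychological feature can still enter through the within-subject comparison. If that route has 80% power and is independent of the first (both assumed), the chance of admission falls from 1 − 0.2 × 0.2 = 96% to 1 − 0.5 × 0.2 = 90%. A social feature has no within-subject route, so the drop from about 80% to about 50% applies to it directly, apart from any support from review evidence.

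**Step 5: power if the contrast is limited to Birmingham cases** (48 controls, d = 0.5, noncentral t):

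| Birmingham cases | Power |
|---|---|
| 48 | 67.9% |
| 96 | 80.2% |
| 150 | 85.1% |

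A regression with group and site terms estimates the group difference from the same Birmingham comparison. Essex cases inform the site term, which is estimable because cases are tested at both sites.

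**The case against.** The strongest reply is that this is a condensed article, that site handling is often left to an analysis plan, and that the article never says the sites are pooled. If the 96 cases are all tested in Birmingham, the problem disappears. That is true, and it is why the point is conditional. It is still more than missing detail: the article fixes a single-site source of controls, names tests that cannot carry a site term, and places no site restriction on the cases.

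A second reply is that a laboratory shift may be small. The article cites high interrater reliability for pressure pain threshold and high reliability for the dynamometer. Much of the battery is questionnaires, motion sensors, electromyography or user-independent cuff algometry. Both sites draw on staff, students and local community. This stands as a reason to expect a modest shift. It does not establish that the mean offset between the two laboratories and populations is zero.

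A third reply concerns harm downstream. Both models are fitted within the recurrent-NP cohort, so a feature admitted in error mainly costs one of about 16 places, and LASSO may remove it. Uniform shrinkage, the stated alternative, would not. This limits the damage to the models, but not to O.1's own reading of the differences as related to neck-pain history.

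A reader might infer that site alone can admit or drop any candidate predictor, with error rates near 30%. The documents do not support that. Such rates need a 0.5 SD shift, as large as the effect the study is powered to detect, and half the cases from Essex. Dropping a physical or psychological feature also requires the within-subject comparison to miss it, and review evidence informs selection as well.

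**Conclusion.** The point holds in a limited form. As written, the O.1 between-group comparison neither restricts nor adjusts for site although all controls come from Birmingham. If Essex cases are included, the contrast carries a bias of the Essex share times the site shift.

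On assumed values, false admission per feature rises from 5% to about 8% or 13%, and there is no effect if there is no shift. The document supplies neither the share nor the shift, so these figures illustrate sensitivity and do not estimate the actual error.

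The confounding is partial, because cases are tested at both sites and site can be separated from group. The risk of losing a feature falls mainly on the social domain. A change is worth making because it is cheap and protects the interpretation of O.1.

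**What to change.** In *O.1 Identification of candidate predictors* and in the O.1 sample size section, state that the between-group comparison sets the 48 controls against recurrent-NP participants tested in Birmingham, using at least 96 of the 300. Alternatively, replace the plain two-sample test by a regression with group and site terms; the Mann-Whitney option cannot take a site term, so a suitable regression would also be needed for non-normal features. In either case, report the Essex-minus-Birmingham difference among cases for each feature as a check. It combines laboratory and population differences and does not separate them.

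The cost is a short change of text and no new data. The downside is fewer cases in the contrast: the planned 80% power at d = 0.5 is kept only if at least 96 Birmingham cases are used. If O.1 stayed at 96 cases in total with half from Essex, power would be 67.9%, so the comparison should draw on the wider cohort. The article does not state how many of the 300 Birmingham will supply; that number needs to be confirmed.
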